#### **6.2.4 Randomization and Allocation**

This study is conducted as part of routine preoperative respiratory rehabilitation under health insurance; participants will perform either sham EMT (control) or EMT (intervention) as a component of the rehabilitation program. After obtaining consent, participants will be randomly assigned using the UMIN medical research support (case registration and allocation) system, cloud version [INDICE cloud]. Allocation factors are: age (<65, ≥65), sex (male/female), and baseline PAS score category: 1–2 (no dysphagia), 3–5 (dysphagia), 6–8 (aspiration). Allocation will be performed using a non-deterministic minimization method. These factors are based on reports indicating associations of age and sex with swallowing function, and to balance baseline swallowing function between groups. The INDICE cloud randomization program will be prepared with data-management support from KHGRAC and managed strictly to prevent external disclosure. Participants and outcome assessors will be blinded to allocation.

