#### **6.4.4 VFSS**

VFSS findings and results obtained at the start of neoadjuvant therapy and postoperatively will be used.

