## **6.5 Endpoints and Assessments**

### **6.5.1 Primary Endpoint**

PAS score on videofluoroscopic swallowing study (VFSS).

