### 8.2 Statistical Analysis

Patients with postoperative recurrent laryngeal nerve palsy will be excluded from analyses. Between-group comparisons will use t-tests for continuous variables and Fisher's exact test or chi-square tests for categorical variables. Statistical significance will be set at  $P<0.05$ .

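### The stated comparison is an unadjusted t-test although allocation is minimised on age, sex and baseline PAS; if those factors are prognostic, the test is conservative and precision is lost

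*Protocol*

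**What the plan says.** Protocol section 8.2 fixes the method in one sentence: "Between-group comparisons will use t-tests for continuous variables", with Fisher's exact or chi-square tests for categorical ones. It mentions no model, covariate, change from baseline or re-randomisation test, and no other section provides for adjustment.

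The sentence does not name PAS. That the t-test is meant for it follows from section 8.1, which sizes the trial on a difference in mean PAS with a common SD.

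Section 6.2.4 describes the allocation: "Allocation will be performed using a non-deterministic minimization method". On the factors it says "Allocation factors are: age (<65, ≥65), sex (male/female), and baseline PAS score category", with PAS grouped as 1–2, 3–5 and 6–8. It gives this reason: "These factors are based on reports indicating associations of age and sex with swallowing function, and to balance baseline swallowing function between groups".

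A baseline value of the primary endpoint exists, because section 6.4.4 states "VFSS findings and results obtained at the start of neoadjuvant therapy and postoperatively will be used".

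**The concern.** The design treats age, sex and baseline swallowing as worth balancing, and the analysis then ignores all three. Minimisation on a prognostic factor removes part of the chance variation in the difference between arms. An unadjusted t-test does not know this: its standard error still contains the variation that the allocation took out. The reported interval is then wider than it should be, and the true type I error falls below the nominal 5%.

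The t-test also leaves unused whatever the baseline PAS explains of the postoperative PAS. Minimisation works on three broad categories, so differences between arms within a category remain, and only adjustment for the score itself can deal with them. With about 17 analysed patients per arm, this information comes at almost no cost.

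**Working it through.** **Inputs from the protocol (section 8.1).** Difference 0.8; common SD 0.8; two-sided alpha 0.05; power 0.80; ratio 1:1; 16 per group before losses; about 5% dropout; about 10% excluded for nerve palsy; target 40.

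**Assumed input.** The correlation ρ between the covariates taken together and postoperative PAS is not in the protocol. The range used is 0 to 0.7.

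**1. The plan's own figure.** With the normal approximation, n per arm = 2 × (1.960 + 0.842)² × (0.8/0.8)² = 15.7, so 16. The stated 16 per group reproduces. With the t distribution, power is 0.781 at 16 per arm and 0.807 at 17.

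**2. Patients analysed.** 40 × (1 − 0.15) = 34, or 40 × 0.95 × 0.90 = 34.2. That is about 17 per arm.

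**3. Power with and without adjustment.** For the t-test, SE = 0.8 × √(2/17) = 0.274, noncentrality = 0.8/0.274 = 2.92, and df = 32, giving power 0.807. For the adjusted model, SE = 0.8 × √(1 − ρ²) × √(2/17) and df = 32 − 3 = 29 (baseline PAS score, age group, sex).

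| ρ | 1 − ρ² | SE | Noncentrality | Power |
|---|---|---|---|---|
| t-test | – | 0.274 | 2.92 | 0.807 |
| 0 | 1.00 | 0.274 | 2.92 | 0.804 |
| 0.2 | 0.96 | 0.269 | 2.98 | 0.82 |
| 0.3 | 0.91 | 0.262 | 3.06 | 0.84 |
| 0.5 | 0.75 | 0.238 | 3.37 | 0.90 |
| 0.7 | 0.51 | 0.196 | 4.08 | 0.98 |

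**4. Does the t-test's standard error match the allocation?** The formula in step 3 treats allocation as independent of the factors, so minimisation was simulated. Settings, all assumed: 34 patients, biased-coin probability 0.8, 60% in one age group, 20% in one sex, PAS categories 70/20/10%, normal outcomes with SD 0.8, and 4,000 trials per setting. R² is the share of outcome variance that the three factors explain. The adjusted model contained PAS category as a score, age group and sex.

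| R² | t-test: mean reported SE | t-test: actual SD of estimate | Type I error, t-test | Type I error, adjusted | Power, t-test | Power, adjusted |
|---|---|---|---|---|---|---|
| 0 | 0.272 | 0.276 | 0.050 | 0.051 | 0.80 | 0.80 |
| 0.10 | 0.272 | 0.266 | 0.049 | 0.054 | 0.81 | 0.82 |
| 0.25 | 0.274 | 0.250 | 0.032 | 0.047 | 0.82 | 0.89 |
| 0.50 | 0.273 | 0.232 | 0.024 | 0.057 | 0.85 | 0.97 |

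SE, SD and type I error come from the runs with no true difference; power comes from the runs with a difference of 0.8. With 4,000 trials, a type I error near 0.05 carries a simulation error of √(0.05 × 0.95/4,000) = 0.003.

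The t-test's standard error is about right up to R² 0.10 and too large from about 0.25. The adjusted model stays near 5% throughout. Minimisation itself gives the t-test a little extra power when the factors are prognostic, so the gain from adjustment is slightly smaller than step 3 suggests.

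**The case against.** The strongest objection is that the benefit rests on a correlation that the protocol does not give. Section 6.2.4 reports associations with swallowing for age and sex only; baseline PAS is there to be balanced. The predictors of postoperative dysphagia named in section 4.0 are nerve palsy and muscle cross-sectional area, and major surgery lies between the two PAS measurements. The correlation could be low, and at R² of 0.10 or less the gain is negligible. This stands, and it is why the range starts at zero.

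It can also be said that an unadjusted t-test is a valid, mildly conservative choice for a 40-patient phase II trial, and that covariates are commonly left to a statistical analysis plan. The first part is true, but the conservatism buys nothing here. The second carries less weight, because section 8.2 states the test, so an analysis plan that adjusted would depart from the protocol.

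The simulation has limits too. It uses normal outcomes for an 8-level score, assumed factor frequencies, and no removal of nerve-palsy cases after allocation, which could disturb the balance. Its figures are illustrative.

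A reader might go on to fault the t-test for treating an ordinal score as interval data. That is not part of this point: the linear model proposed here makes the same assumption, so the remedy would not answer the criticism.

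**Conclusion.** The point holds in a conditional form. Section 8.2 specifies an unadjusted comparison after an allocation minimised on three factors, one of them the baseline of the primary endpoint. If those factors predict postoperative PAS, the t-test is conservative and loses precision. If they do not, nothing is wrong with it.

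The size depends on the assumed correlation. At the protocol's difference and SD with 17 per arm, adjustment changes power from 0.807 to between 0.804 (correlation 0) and 0.98 (correlation 0.7). The effect is material from an R² of about 0.25.

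Two stronger conclusions might be inferred and are not supported. The mismatch does not produce false positives or bias: in the simulation the t-test's error rate stays at or below about 5%. Nor does it show the sample size to be wrong: the 16 per group reproduces, and under the protocol's own assumptions the t-test has about 80% power at the expected number analysed. This is an improvement that should be made, not a defect that invalidates the trial.

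**What to change.** In section 8.2, state that the primary analysis is a linear model of postoperative PAS on treatment, with baseline PAS (the score, not the category), age (<65/≥65) and sex as covariates, reporting the adjusted mean difference with its 95% confidence interval. Keep the unadjusted t-test as a sensitivity analysis, optionally with a re-randomisation test that repeats the minimisation. For the continuous secondary endpoints, use the baseline value of each as a covariate.

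The wording must name the postoperative time point to be modelled. Sections 6.4.4 and 6.5.1 do not fix one, and the schedule in 6.6.1 has no row for videofluoroscopy.

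The cost is a change of wording and three degrees of freedom, about 0.003 of power (0.807 to 0.804) if the factors are not prognostic. No new data are needed. The change should be made before anyone sees outcome data by arm.

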##### **Preoperative respiratory rehabilitation (during neoadjuvant therapy period)**

###### **Control group (Sham EMT):**

- Device instruction and load adjustment during the neoadjuvant therapy period
- Expiratory load fixed at the minimum device setting: 10 cmH2O
- 30 breaths per set; 2–3 sets/day; completion criterion: ≥5 days/week

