### **6.5.2 Secondary Endpoints**

- Repetitive Saliva Swallowing Test (RSST)
- Functional Oral Intake Scale (FOIS)
- Maximum tongue pressure
- Ultrasound measures: laryngeal elevation distance; suprahyoid muscle cross-sectional area

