### 6.6.1 Assessment Schedule

| Assessment                            | Baseline
(1–2
days
before
surgery?) | Start of
neoadjuvant
therapy | Preoperative | Post-
op day
10 $\pm$ 4 | Post-
op 1
mo $\pm$ 7
d | Post-
op 3
mo $\pm$ 7
d | Post-
op 6
mo $\pm$ 7
d |
|---------------------------------------|-------------------------------------------------|------------------------------------|--------------|-------------------------------|----------------------------------|----------------------------------|----------------------------------|
| Informed
consent                   | —                                               | •                                  | —            | —                             | —                                | —                                | —                                |
| Respiratory
muscle
strength*1   | —                                               | •                                  | •            | $\Delta$ *2                   | •                                | •                                | •                                |
| Swallowing
screening*1             | —                                               | •                                  | •            | $\Delta$ *2                   | •                                | •                                | •                                |
| Tongue
pressure*1                  | •                                               | •                                  | •            | •                             | •                                | •                                | •                                |
| Ultrasound
swallowing
muscles*1 | •                                               | •                                  | •            | •                             | •                                | •                                | •                                |

|                                   |   |   |   |     |     |     |     |
|-----------------------------------|---|---|---|-----|-----|-----|-----|
| Appendicular skeletal muscle mass | ● | ● | — | ●   | ●   | ●   | ●   |
| Exercise capacity                 | ● | ● | — | △*2 | △*2 | △*2 | △*2 |

\*1 Assessments are performed by research staff blinded to participant allocation.

\*2 Performed only when approved by the attending physician.

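### For three secondary endpoints measured repeatedly, section 8.2 names only unadjusted t-tests, which use neither the start-of-therapy value nor the other visits

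*Protocol*

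**What the plan says.** Protocol section 6.5.2 lists among the secondary endpoints "Maximum tongue pressure" and "Ultrasound measures: laryngeal elevation distance; suprahyoid muscle cross-sectional area". All three are continuous.

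In the schedule (6.6.1), the rows "Tongue pressure*1" and "Ultrasound swallowing muscles*1" are marked in every column. One mark falls at the start of neoadjuvant therapy and five come later: preoperative, day 10, and 1, 3 and 6 months after surgery. Unlike some other assessments, these marks do not depend on the attending physician's approval.

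Training belongs to the neoadjuvant period (6.2.5, under "Preoperative respiratory rehabilitation (during neoadjuvant therapy period"), and the same section rules out EMT after surgery until 6 months.

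Section 8.2 gives the method: "Between-group comparisons will use t-tests for continuous variables", with Fisher's exact or chi-square tests for categorical variables and one significance level. It names no analysis visit, no use of the start-of-therapy value and no model for repeated measurements.

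**The concern.** The data are longitudinal with a pre-training value, but the only stated method is a comparison of two independent samples. Applied at a visit, it treats that visit as if nothing else were known about the patient. The between-patient variation that the start-of-therapy value would explain stays in the error term, the other visits add no precision, and a patient who missed that visit drops out of the comparison.

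Section 6.5.2 gives these measures the role of helping to interpret how EMT affects swallowing, and section 10.4 says that the ultrasound is the only assessment done solely for the study. In a 40-patient trial meant to inform a multicentre study, imprecise estimates here weaken the explanation of whatever the PAS comparison shows.

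The point concerns these three secondary endpoints only, not the primary PAS comparison.

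**Working it through.** **The plan's own figure.** Section 8.1 takes a PAS difference of 0.8 and SD 0.8 (1.0 SD), two-sided 0.05 and power 0.80, and reports 16 per group. The normal approximation gives 16 (power 0.807). The exact noncentral t gives 0.781 at 16 and 0.807 at 17. Allowing for 5% dropout plus 10% nerve-palsy exclusion, 32/0.85 = 37.6 (38) and 34/0.85 = 40. The stated 40 reproduces. Evaluable patients: 40 × 0.85 = 34, or 17 per arm.

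**Inputs that the protocol does not give.** No effect size, SD or within-patient correlation is stated for tongue pressure or ultrasound. I work in SD units and assume equal variances and one correlation ρ between all visits, including the start-of-therapy value (compound symmetry), with ρ = 0.5 and 0.7 as main cases.

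**Variance relative to a t-test at one visit**

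- One visit, adjusted for the start-of-therapy value: 1 − ρ²
- Mean of four postoperative visits, unadjusted: (1 + 3ρ)/4
- Mean of four, adjusted: (1 + 3ρ)/4 − ρ²

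A single-visit t-test with 17 per arm has 80% power at 0.99 SD. Each other detectable difference is about 0.99 × √(variance factor); losing one degree of freedom for the covariate changes it by about 0.001 SD or less.

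| Analysis | Factor, ρ = 0.5 | Detectable | Factor, ρ = 0.7 | Detectable |
|---|---|---|---|---|
| t-test, one visit | 1 | 0.99 SD | 1 | 0.99 SD |
| One visit + start-of-therapy value | 0.75 | 0.86 SD | 0.51 | 0.71 SD |
| Mean of four postoperative visits | 0.625 | 0.78 SD | 0.775 | 0.87 SD |
| Mean of four + start-of-therapy value | 0.375 | 0.61 SD | 0.285 | 0.53 SD |

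**Do the extra visits add anything once the start-of-therapy value is used?** Yes. The ratio (1 − ρ²)/[(1 + 3ρ)/4 − ρ²] is 2.4, 2.0, 1.8 and 1.65 at ρ = 0.3, 0.5, 0.7 and 0.9.

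**How much does an unadjusted average gain alone?** For an illustrative constant effect of 0.8 SD, power is 62% at one visit. For the four-visit mean it is 91%, 82%, 77%, 73% and 65% at ρ = 0.3, 0.5, 0.6, 0.7 and 0.9. The gain is always positive under a constant effect, but small at high correlation.

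**If the effect wanes.** Suppose that it runs 0.8, 0.6, 0.4 and 0.2 SD from day 10 to 6 months. The average is (0.8 + 0.6 + 0.4 + 0.2)/4 = 0.5 SD.

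| Power | ρ = 0.5 | ρ = 0.7 |
|---|---|---|
| Day-10 t-test | 62% | 62% |
| Four-visit mean | 43% | 36% |
| Day 10 + start-of-therapy value | 74% | 89% |
| Four-visit mean + start-of-therapy value | 64% | 75% |

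So the averaging gain can reverse, while the gain from the start-of-therapy value remains.

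**The case against.** The strongest reply is that section 8.2 does not confine the analysis to one visit. T-tests could be run at every visit, on change scores, or on each patient's mean over visits. The averaging gain above is itself obtained with a two-sample comparison of means. An analysis plan that is not shown could settle the visit and the summary.

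Part of this stands. A reader might infer that the protocol discards most of the data and most of the power. The documents do not support that. Visit-by-visit t-tests would use every measurement somewhere. Against the four-visit mean, the single-visit test keeps 62/82 = 76% of the power at correlation 0.5, 62/73 = 85% at 0.7, and 62/65 = 95% at 0.9.

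The reply does not remove the point. Each visit-by-visit test still detects only 0.99 SD and still loses patients who missed that visit. Five such tests also give no single answer per endpoint, and up to 1 − 0.95⁵ = 22.6% chance of at least one false positive if they were independent. The method is stated rather than left open, so a later mixed model would depart from the protocol text.

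Three further cautions hold. Training stops before surgery, so a constant postoperative effect cannot be taken for granted. The heading of the first schedule column carries an unresolved query about its timing, so the visit count is not beyond doubt; I count only the five clearly labelled later visits. And the sample size was set for PAS alone, so no power is promised for these endpoints.

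**Conclusion.** The point holds as one of efficiency on secondary endpoints. Unadjusted t-tests are a weaker choice than a repeated-measures model with the start-of-therapy value, and the data for the better analysis are already being collected.

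With 17 evaluable per arm, the detectable difference at a single visit falls from 0.99 SD to about 0.86 SD (correlation 0.5) or 0.71 SD (correlation 0.7) through the start-of-therapy value alone. For the postoperative average with that value it falls to about 0.61 or 0.53 SD. These figures rest on assumed correlations and compound symmetry; the last pair also needs a similar effect across the four postoperative visits. If the effect wanes, the average should not carry the conclusion, which is why the per-visit contrasts matter. This should be changed before analysis, but it does not threaten the primary comparison.

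**What to change.** In section 8.2, for maximum tongue pressure, laryngeal elevation distance and suprahyoid muscle area, replace the t-test with one linear mixed model per endpoint:

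- outcome at the preoperative visit, day 10, and 1, 3 and 6 months;
- fixed effects for visit, treatment, treatment-by-visit and the start-of-therapy value;
- one covariance structure named in advance and suited to about 34 patients (an unstructured matrix over five visits has 5 × 6/2 = 15 parameters, so a more economical structure such as compound symmetry is easier to support);
- Kenward-Roger degrees of freedom.

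Report, with 95% confidence intervals, the preoperative contrast (the direct training effect) and each postoperative contrast. Give the postoperative average as a summary beside them, not in their place. Confirm in the schedule which column supplies the pre-training value.

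The cost is one paragraph and slightly more analysis work. No new data or patients are needed. The downside is reliance on a covariance assumption.

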### 8.3 Definitions

#### 8.3.1 Outcomes

| Outcome                   | Definition                        | Censoring date |
|---------------------------|-----------------------------------|----------------|
| Swallowing function score | PAS score on VFSS (8-point scale) | —              |
| Aspiration incidence      | PAS score $\geq 6$ on VFSS        | —              |

#### 8.3.2 Adverse Events

Definitions:

Serious: falls/fractures, cardiopulmonary arrest, death.

Non-serious: hypotension, unsteadiness, dizziness, malaise.

Known: dyspnea, anxiety, palpitations, lower-limb fatigue.

Causality: Adverse events occurring during study procedures (assessment/measurement) are considered related.

Follow-up items when an adverse event occurs: symptoms/findings, onset date, outcome (A=recovered; B=improved; C=unchanged; D=recovered with sequelae; E=death), and outcome date.

Reporting: In the event of a serious or unexpected adverse event, the Principal Investigator will report to the Dean in accordance with institutional regulations. If an adverse event meets criteria for urgent reporting, sub-investigators will immediately notify the Principal Investigator.

Depending on frequency and severity, enrollment may be suspended or the trial interrupted/terminated at the discretion of the study leadership.

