## 4.0 Background and Rationale

Esophagectomy with reconstruction is a highly invasive curative treatment for esophageal cancer. Surgery-related complications after esophagectomy include pulmonary complications, anastomotic leakage, anastomotic stricture, recurrent laryngeal nerve palsy, and dysphagia. In our institutional data, the postoperative pneumonia rate decreased from 25.9% (through fiscal year 2019, predominantly open thoracotomy) to 18.0% (fiscal years 2020–2023, after transitioning to minimally invasive approaches), suggesting that postoperative pulmonary complications (PPCs) are declining with less invasive surgery (unpublished data). However, postoperative dysphagia after esophagectomy has remained relatively constant at approximately 15% in our data from fiscal years 2016–2023 (unpublished data).

Prior research in esophageal cancer patients undergoing esophagectomy has reported that recurrent laryngeal nerve palsy (OR 6.6, 95% CI 1.30–33.8) and preoperative CT-measured suprahyoid/geniohyoid muscle cross-sectional area (OR 3.6, 95% CI 1.16–11.1) are significant predictors of postoperative dysphagia. In addition, preoperative tongue pressure, an index of suprahyoid and swallowing-muscle strength, has been reported as a predictor of aspiration pneumonia after esophagectomy. Furthermore, laryngeal elevation is known to significantly influence swallowing after esophagectomy, and reduced laryngeal elevation distance on postoperative videofluoroscopic swallowing studies has been associated with aspiration.

Expiratory muscle training (EMT), which applies expiratory resistance during exhalation, has been investigated as an intervention for dysphagia. Because EMT induces activity in orofacial and pharyngeal muscles (e.g., submandibular, palatal, lingual, and pharyngeal muscles), it may improve muscle strength and cross-sectional area, contribute to the coordination of bolus transport, maintain swallowing safety and efficiency, and lead to functional improvement. A meta-analysis of randomized controlled trials in stroke patients reported that EMT improved the PAS score by  $-0.81$  (95% CI  $-1.19$  to  $-0.43$ ;  $I^2=39\%$ ;  $P<0.0001$ ). EMT is believed to enhance muscular and neural adaptations relevant to swallowing recovery, with direct effects in reducing aspiration and pharyngeal residue.

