#### **6.2.2 Exclusion Criteria**

- Planned two-stage esophageal reconstruction or planned total laryngectomy
- Meets contraindications for EX-1 Medic® EMT device, including: frequent asthma exacerbations; tympanic membrane perforation or similar injury; markedly elevated LV end-diastolic volume/pressure; worsening (or high likelihood) of heart failure signs/symptoms after respiratory muscle training per physician judgment; history or suspected costochondritis
- Active infection or other serious comorbidity such that EMT may increase dyspnea due to respiratory muscle fatigue, reduce consciousness due to hyperventilation, or cause syncope due to rapid hemodynamic changes associated with intrathoracic pressure shifts, as judged by the attending physician
- Difficulty enrolling due to disorientation or psychiatric illness
- High risk of pneumothorax or high physical burden from EMT due to severe emphysematous lesions or giant bullae, judged by investigators prior to surgery
- Serious conditions such as severe pneumonia, heart disease, severe liver disease, severe kidney disease; history of cardiac complications within 1 month (unstable angina, myocardial infarction, percutaneous coronary intervention, coronary artery bypass grafting) or cerebrovascular disease within 6 months; or severe emphysema/giant bullae

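### Seriousness in section 8.3.2 is defined by event name rather than by outcome, so EMT hazards named in section 6.2.2 are misclassified and a life-threatening known event has no explicit trigger for the report to the Dean

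*Protocol*

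**What the plan says.** Section 8.3.2 (Adverse Events) sorts events into three lists of names:

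- "Serious: falls/fractures, cardiopulmonary arrest, death"
- "Non-serious: hypotension, unsteadiness, dizziness, malaise"
- "Known: dyspnea, anxiety, palpitations, lower-limb fatigue"

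Nothing marks the names as examples, and no list refers to outcome, hospitalisation or threat to life. The reporting rule follows: "In the event of a serious or unexpected adverse event, the Principal Investigator will report to the Dean in accordance with institutional regulations". A further sentence has sub-investigators notify the Principal Investigator at once when criteria for urgent reporting are met, but the protocol does not give those criteria. On suspension it says: "Depending on frequency and severity, enrollment may be suspended or the trial interrupted/terminated at the discretion of the study leadership". The items recorded for each event are symptoms or findings, onset date, a five-level outcome code and outcome date.

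Section 6.2.2 (Exclusion Criteria) shows which harms the authors had in mind. It excludes patients in whom EMT may worsen dyspnea, reduce consciousness or "cause syncope due to rapid hemodynamic changes associated with intrathoracic pressure shifts". It also excludes those at high risk of pneumothorax and those whose heart failure may worsen with respiratory muscle training.

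**The concern.** Seriousness usually depends on what an event does to the patient. Here it depends on what the event is called. A harmless fall is serious by name, while hypotension needing intensive care is non-serious by name. The hazards screened for in section 6.2.2 do not appear on the serious list at all.

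Two things are at stake. The first is participant safety during conduct, because the seriousness label is one of the two triggers for the report to the Dean. The second is the safety record. Section 5.0 uses this trial to design a multicentre study, and a low count of serious events under this definition could be read as reassurance that it does not give.

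**Working it through.** No arithmetic is involved. The check applies the three lists and the reporting trigger of section 8.3.2 to each hazard that section 6.2.2 attributes to EMT or respiratory muscle training.

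**Inputs.** The three lists and the trigger come from section 8.3.2, and the five hazards from section 6.2.2. The other device contraindications there (frequent asthma exacerbations, tympanic membrane injury, costochondritis) are left out, because they are pre-existing conditions and not stated effects of training.

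**Reading applied.** The serious list is taken as closed, since nothing marks it as illustrative. An event on the known list is taken as not unexpected; an event absent from it is taken as unexpected.

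| Hazard in 6.2.2 | Serious list | Non-serious list | Known list | Classed serious? | Report to the Dean? |
|---|---|---|---|---|---|
| Dyspnea | no | no | yes | only if a listed event follows | only if a listed event follows |
| Reduced consciousness | no | no | no | only if a listed event follows | yes, as unexpected |
| Syncope | no | no | no | only if a listed event follows | yes, as unexpected |
| Pneumothorax | no | no | no | only if a listed event follows | yes, as unexpected |
| Worsening heart failure | no | no | no | only if a listed event follows | yes, as unexpected |

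A listed event here means a fall or fracture, a cardiopulmonary arrest or a death.

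**Result.** None of the five hazards is on the serious list, and one (dyspnea) is on any list. Four are misclassified but still reported. One is neither classed as serious nor reported to the Dean on the stated trigger. Palpitations, which section 6.2.2 does not name, are listed as known and fall into the same gap as dyspnea.

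**Does anything else in the protocol close the gap for known events?**

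- The urgent route in section 8.3.2 leads to the Principal Investigator, and its criteria are not stated.
- Section 10.5 requires an annual progress report and a report on facts that undermine the study's ethical or scientific basis or may affect its continuation. These are general duties, not triggers tied to an event.
- Section 11.4 rules out monitoring and audit.

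None of these reliably catches a severe known event.

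**Suspension rule.** It relies on frequency and severity, but the recorded items include no severity grade. Severity would have to be inferred from the free description and the outcome code.

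**The case against.** The strongest reply is that the reporting trigger has two parts, and the second does most of the work. Pneumothorax, syncope, reduced consciousness and worsening heart failure are not on the known list, so they go to the Dean as unexpected. By the same logic so would postoperative pneumonia. This stands, and it confines the reporting gap to known events.

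A reader might infer that the named hazards can never be serious. The text does not support that: syncope with a fall, dyspnea ending in arrest, or any fatal event is on the serious list. Hypotension that causes a fall also becomes serious through the fall.

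A reader might also infer that severe dyspnea would lead to no report of any kind. That goes too far. The urgent route exists, section 10.5 could apply, and the report to the Dean is made under institutional regulations that are not reproduced and may carry their own definition of seriousness. What can be said is that this protocol states no trigger that such an event meets. If the regulations do define seriousness by outcome, the name list in section 8.3.2 conflicts with them and still needs correcting.

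It is fair, too, that known describes expectedness and not grade, and that dyspnea is on neither the serious nor the non-serious list. Strictly it is unclassified, and it is not serious only because the serious list is closed. The document derives from a Japanese source, so the intent behind the list is not certain. Both points argue for clearer wording, not for leaving it as it is.

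Finally, the pneumonia rate in section 4.0 may tempt a reader to put a number on the problem. It does not measure it: it is background surgical risk that applies to both arms, and it does not say how many cases would meet an outcome-based definition.

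**Conclusion.** The point holds in this form. Section 8.3.2 states a rule that misclassifies events; this is not detail left for an analysis plan. For four of the five EMT hazards in section 6.2.2 the consequence is a wrong label, with reporting preserved. For dyspnea, and for palpitations, a life-threatening case meets neither part of the trigger for the report to the Dean unless a listed event follows, and nothing else stated in the protocol reliably fills the gap.

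The conclusion assumes that the serious list is closed, that the known list defines what is expected, and that the unshown institutional regulations do not override section 8.3.2. No sample size, power or error rate is affected. The number of events that would be missed or mislabelled cannot be estimated from the document. The matter still deserves correction now: it concerns participant safety during conduct, and reports not sent at the time cannot be restored later.

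**What to change.** In section 8.3.2:

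1. Define as serious any event that is fatal, is life-threatening, requires or prolongs hospitalisation, or causes lasting disability, whatever its name. Keep the present names as examples.
2. State that an event on the known list or the non-serious list that meets these criteria is serious and is reported to the Dean.
3. Reconcile the three lists with the hazards named in section 6.2.2.
4. State the criteria for the urgent route to the Principal Investigator, or cite the regulation that contains them.

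Optionally, add a severity grade to the recorded items, since suspension is said to depend on severity.

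The cost is an amendment to the wording and, if the option is taken, one more field on the adverse-event form. It needs no extra patients or procedures. The downside is that more events after esophagectomy will be classed as serious and need reporting.
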